**PRECIS:**

This protocol describes a randomized, phase II study of subcutaneous interleukin-2 (IL-2) therapy in HIV disease. The primary objectives of this protocol are to demonstrate the safety and tolerance of IL-2 in the absence of concomittant antiretrovirals, to demonstrate the immunological efficacy of IL-2 in the absence of antiretroviral therapy as defined by increases of CD4+ cell counts from baseline and to examine the effects of IL-2 on measures of plasma HIV-RNA as defined by changes from baseline. Approximately 36 patients with HIV infection, >350 CD4+ cells/mm3 and no history of opportunistic infection will be required to complete the trial. Individuals with no prior or current use of antiretroviral drugs will be able to participate in the study. Eligible patients will be randomly assigned to receive either no therapy or subcutaneous IL-2 at one of two doses every 12 hours for 5 days every 8 weeks. The two dose levels of IL-2 that will be studied are 4.5, and 7.5 million units (MIU) of IL-2. One group will receive 4.5 million units q12h x 5 days every eight weeks. An additinal group will receive 7.5 MIU q12h x 5 days every eight weeks. Following the completion of this study, patients randomized to receive IL-2 will be able to continue receiving IL-2 during follow-up or as a part of an additional protocol that will be based on the results of the current study. It is anticipated that this study will be a phase III trial involving a total of 3700 patients worldwide.

Table of contents

APPENDICES

I. SYNOPSIS

II. INTRODUCTION

III. RATIONALE

IV. OBJECTIVES

V. STUDY DESIGN

VI. PATIENT SELECTION

VII. TREATMENT PROCEDURES

VIII. STUDY PROCEDURES

IX. STUDY WITHDRAWAL

X. TRIAL MANAGEMENT

XI. ADVERSE EVENTS AND MANAGEMENT

XII. INSTITUTIONAL REVIEW BOARD APPROVAL/ETHICS COMMITTEE ACCEPTANCE

XIII. INFORMED CONSENT

XIV. COMPENSATION, INSURANCE AND INDEMNITY

XV. PROTOCOL AMENDMENTS

XVI. DRUG ACCOUNTABILITY

XVII. LABORATORY REQUIREMENTS

XVIII. CASE REPORT FORMS

XIX. STUDY MONITORING

XX. RETENTION OF RECORDS

XXI. USE OF INFORMATION AND PUBLICATION

XXII. REFERENCES

# I. SYNOPSIS

This protocol describes a randomized, phase II study of subcutaneous interleukin-2 (IL-2) therapy in HIV disease. There are three primary objectives:

1. to demonstrate the safety and tolerance of IL-2 in the absence of concomittant antiretrovirals.

2. to demonstrate the immunological efficacy of IL-2 in the absence of concomittant antiretroviral therapy as defined by increases of CD4+ cell counts from baseline.

3. To assess the effects of IL-2 in the absence of concomittant antiretroviral therapy on plasma HIV RNA levels as defined by changes from baseline.

Approximately 36 patients with HIV infection, > 350 CD4+ cells/mm3 and no history of opportunistic infection will be required to complete the trial. Individuals never previously treated with antiretrovirals will be eligible to participate. Eligible patients will be randomly assigned to receive one of two treatment regimens:

A. No therapy (n=12)

B. Subcutaneous IL-2 at one of 2 doses, q12h x 5 days every 8 weeks (n=24)

Two different dose levels of IL-2 will be studied. The first group will receive 4.5 million units (MIU) q12h x 5 days every eight weeks. The second group will receive 7.5 MIU q12h x 5 days every eight weeks. Following the completion of this study, continued treatment for all patients will be made available through an additional protocol that will be based upon the results of the current study. It is anticipated that this additional study will be a phase III trial involving a total of 3700 patients worldwide.

# II. INTRODUCTION

The clinical management of HIV disease relies upon the use of antiretroviral and antimicrobial chemotherapies. Antimicrobial agents are used to treat or suppress episodes of infectious disease arising from the profound immunodeficiency that characterizes HIV disease. Antiretroviral drugs, through inhibition of HIV replication, delay the progressive depletion and destruction of immunocompetence. Even at the time of maximal antiretroviral activity with these agents it is often possible to detect virus replication. Furthermore, HIV with reduced susceptibility to these agents can be isolated from patients who have received therapy for relatively short periods of time. Ultimately, in some patients continued use of antiretroviral chemotherapy no longer results in significant suppression of virus replication and destruction of the immune system continues unchecked. The purpose of the present study is to determine whether or not IL-2 could be an alternate strategy for treatment in patients with relatively early HIV disease who do not wish to commence antiretroviral therapy.

### A. INTERLEUKIN-2 IN HIV DISEASE

Interleukin-2 is a 15Kdalton, immunostimulatory protein produced in vivo by T-lymphocytes following activation by antigens. It is central to the appropriate responsiveness of the immune system challenged by invading pathogens. Its synthesis and release by CD4+ T-lymphocytes in particular, is of critical importance to the orchestrated events that follow detection of foreign antigen and lead to clearance of pathogen and resolution of disease. IL-2 results in the proliferation and maturation of both T- and B- lymphocytes (Smith, 1988). In vitro, exogenous IL-2 can enhance the NK and CTL activity of lymphocytes from patients with AIDS (Rook et al, 1985).

Immunotherapy of HIV disease with IL-2 has undergone considerable investigation in Phase I and II trials. These studies have defined the safety profile of IL-2 delivered in a number of different regimens as well as the virological and immunological changes resulting from treatment.

Initial Phase I studies were conducted in AIDS patients with KaposiÕs sarcoma. Purified, native IL-2 was administered by continuous intravenous infusion (CIV) for 5 days a week for four consecutive weeks at doses ranging from 250 to 250,000 units per day (Lane et al, 1984). In a second group of 21 patients recombinant IL-2 was administered by CIV for 5 days every eight weeks at doses ranging from 1,500 Units to 12.5 MIU per day (Murphy et al, 1988). In these studies toxicities were minimal and included hepatic dysfunction, febrile illness, eosinophilia, mild prolongation of PTT and proteinuria. There was an increase in the incidence of bacterial infections compared with patients receiving g-interferon. Although treatment did not result in consistent clinical responses in patients with late-stage HIV disease, there was a consistent increase (up to five-fold) in circulating lymphocyte counts.

Additional research undertaken at the National Institutes of Health demonstrated that administration of CIV interleukin-2 at 12-18 MIU/day for 5 days every eight weeks in combination with antiretroviral therapy in patients with more than 200 CD4+ cells/mm3 prior to commencing treatment resulted in significant increases in CD4+ cell counts for up to 4 years (Kovacs et al, 1995a). In 6 of 10 such patients, the magnitude of the CD4+ cell increase was 50% or greater. In the 6 patients with 100-200 CD4+ cells/mm3 before therapy, more frequent dose reductions were required and only two individuals demonstrated more than a 50% increase in CD4+ cell count. In patients with fewer than 100 CD4+ cell/mm3, none experienced a significant increase in CD4+ cell count after therapy. Long-term follow-up of these 10 patients is shown in Figure 1.

In many patients a burst of HIV viremia was observed at the completion of each treatment cycle. Changes in HIV virus load (as measured by branched chain DNA analysis) over the entire study period were consistent with immunological changes. Patients with increased CD4+ cell counts had stable virus load during and after therapy, patients in whom no demonstrable increases in CD4+ cell number were observed had increases in virus load over time.

Additional immunological responses to therapy that were noted in this study included reductions in expression of HLA-DR on CD8+ T-lymphocytes, increases in the expression of CD25 on CD4+ T-lymphocytes and Vb-subset data indicating that the CD4+ cell expansion was polyclonal.

Figure 1.

Kovacs and colleagues (1995b) have recently completed a randomized, controlled trial of CIV IL-2 in patients with HIV infection and more than 200 CD4+ cells/mm3. IL-2 was administered for 5 days every 8 weeks for 10 months. Recipients of antiretroviral therapy alone (n=29) demonstrated a mean reduction in CD4+ cell count of approximately 5 cells mm3/month over 14 months of study (Figure 2).

Figure 2.

Over the same time period, recipients of CIV IL-2 (n=30) experienced a mean increase in CD4+ cell count of approximately 37 cells mm3/month (p<0.001). During the study HIV virus load was determined at monthly intervals (Figures 3a and 3b). At the end of the study, the levels of virus in recipients of IL-2 were not different from baseline levels nor were they different from levels in patients receiving antiretroviral therapy alone.

Figure 3a.

Figure3b.

In total therefore, some 157 patients have been enrolled in randomized comparisons of antiretroviral therapy versus antiretrovirals plus 5-day CIV IL-2. In the period of time during which patients continued to receive randomly allocated study medication, there was a consistent significant increase in CD4+ cell counts for patients receiving the combination. Longer term follow-up of these patients is compromised by the fact that in all trials, patients were allowed to receive open label IL-2 after 6 cycles. Nonetheless, as demonstrated in Table 1 the group of patients initially randomized to receive 5-day CIV IL-2 in combination with antiretrovirals has experienced fewer opportunistic infections than patients initially assigned to receive antiretroviral therapy alone. In addition all of the opportunistic infections have occurred at CD4+ cell counts that are expected for the natural history of HIV disease.

### B. SUBCUTANEOUS (SC) IL-2

Despite the ability to administer CIV IL-2 safely to HIV-infected individuals, it is likely that such a regimen will be inappropriate for widespread clinical use. A less intrusive regimen of IL-2 would afford greater scope for clinical utility. The administration of IL-2 by subcutaneous injection has been evaluated in a number of clinical trials. One study, originally enrolling 18 patients and since amended to recruit a further 48 subjects with CD4+ cell counts >500 cells/mm3 is ongoing. The maximal tolerated dose of SC IL-2 was 15 MIU/day administered for five days every 8 weeks. Toxicities were similar, although generally less severe, to those observed with administration of CIV IL-2. Most patients also experienced local reactions characterized by erythema, tenderness and occasional nodularity. In common with observations derived from studies of CIV IL-2 in HIV disease an analysis of data from the original 18 patients has revealed the following trends: patient tolerance is directly related to HIV disease stage, higher baseline CD4+ counts are predictive of greater CD4+ increases in response to therapy and a favorable CD4+ response is generally disclosed within the first three treatment cycles (Figure 6).

Figure 6.

Twice daily SC dosing for 5 days of a four-week cycle has been evaluated in a five-arm Phase II trial conducted by community-based practitioners and sponsored by Applied Immune Sciences (AIS, Santa Clara, California). Patients in this trial were randomized to receive either 2MIU m2/dose (low dose) or 4 MIU m2/dose (high dose), twice daily with or without ex vivo expanded CD8+ T-lymphocytes for a total of 5 cycles (Deresinski et al, 1995). A total of 23 patients received IL-2 alone under this protocol. The study was controlled with a treatment arm of antiretroviral therapy alone. Toxicities from this trial were relatively mild and related to flu-like symptoms common to nearly all IL-2 regimens. One asplenic patient died following pneumococcal sepsis one week after completion of therapy. The contribution of IL-2 to this even is not known. Transient increases in HIV virus load were noted at day 5 of therapy (2-3 fold increases), although upon completion of study, levels of plasma HIV-RNA were not significantly greater than baseline levels. Recipients of low-dose IL-2 had a mean increase in CD4+ cell count of 34% (range -27 to 93) and recipients of high dose IL-2 had a mean increase of 38% (range -28 to 112). The absence of a dose response is thought to reflect the extent of dose reductions undertaken in the high-dose recipients. Increments in CD4+ cell count were seen in patients with CD4+ cell counts both above and below 350 cells/mm3 suggesting that a subcutaneous regimen might be applicable for patients with more advanced HIV disease.

### C. CONCLUSION

A total of three randomized phase II trials have been conducted that include as comparators both an antiretroviral therapy arm and a 5-day every 8 weeks CIV IL-2 treatment arm. These have yielded consistent data including significant increases in CD4+ cell count in the absence of sustained increases of virus load. A phase III clinical efficacy trial is the next step in determining the true clinical benefit of interleukin-2 therapy in HIV disease. Such a trial will recruit a large cohort of HIV infected patients with early HIV disease in a multinational collaboration. As a prelude to this undertaking a series of phase II studies will be undertaken to support the establishment of a phase III program in settings where IL-2 has not been used or to address specific questions of clinical importance related to the design of such a clinical endpoint trial.

It has also been proposed treatment with IL-2 therapy in the absence of concomittant antiretroviral drugs might be one strategy for the clinical management of patients with early HIV disease. There are no clinical data to determine the validity of this approach. This protocol will generate data on the use of IL-2 in patients with early HIV disease who do not wish to commence regimens of antiretroviral therapy.

# III. RATIONALE

Interleukin-2 administered subcutaneously results in increases in CD4+ cell count that might impact upon HIV disease progression. A phase III trial, recruiting large numbers of HIV positive patients is the next step in the development process. The effects of SC IL-2 in patients with HIV disease in the absence of antiretroviral therapy are not defined. To develop appropriate clinical experience with this approach, this phase II trial will allow administration of IL-2 without antiretroviral therapy to a small number of patients in sites wishing to participate in the phase III protocol.

# IV. OBJECTIVES

This study has three primary objectives: to demonstrate the safety and tolerability of subcutaneously administered IL-2 (at escalating doses delivered for 5 days every eight weeks) in the absence of concomittant antiretrovirals and to demonstrate the immunological efficacy (as demonstrated by increases in CD4+ cell count) and effects upon plasma HIV-RNA levels of SC IL-2 therapy relative to patients treated with no therapy.

Secondary objectives will also be addressed. These will include, assessments of infrastructure requirements, rate of patient recruitment, quality of clinical data and compliance with protocol.

# V. STUDY DESIGN

### A. OVERVIEW

This is a phase II open label study of escalating doses of subcutaneous (SC) IL-2 alone versus no therapy in patients with HIV infection and a CD4+ lymphocyte count of at least 350 cells/mm3. This protocol is intended to define the safety and tolerability, immunological superiority and virological neutrality of IL-2 immunotherapy over no therapy.

There will be 3 treatment arms (1 control; 2 IL-2). Eligible patients will be randomized to receive no therapy or IL-2 therapy with two discreet doses of SC IL-2 (delivered for five days every eight weeks).

A total of 36 patients will be required to complete a minimum of three cycles of treatment. Of these patients, 12 will be allocated to receive no therapy and 24 patients will receive SC IL-2. A cycle is defined as 8 calendar weeks to include as necessary one five day period of SC IL-2 therapy.

Dosing with SC IL-2 will commence at doses of 4.5 MIU or 7.5 MIU twice daily (q12h) for 5 days every eight weeks. No patient will be treated with more than 7.5 MIU q12h x 5 days every eight weeks and no patient will commence a treatment cycle at a dose of less than 1.5 MIU q12h x 5 days every eight weeks.

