### E. Statistical considerations

### 1. Endpoints

The primary endpoint will be the time-weighted mean change in CD4+ cell count from baseline and time-weighted mean change in plasma HIV-RNA from baseline.

Secondary endpoints will include safety data.

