### 2. Sample size

Based on an estimate of within patient variability corresponding to a standard deviation of 150 cells/mm3 (data on file), and using a two-sided significance level of 5%, a total of 36 patients randomized in the ratio of 2 SC IL-2:1 control participant will give 80% power of detecting an increase in the SC IL-2 group of 150 cells/mm3 (175 cells/mm3 with 20% dropout).

Based upon an estimate of within patient variability corresponding to a standard deviation of 0.7 log copies/ml (Eron J et al, NEJM 1995; 333:1662-9), and using a two sided significance level of 5%, a total of 36 patients randomised in the ratio of 2 SC IL-2: 1 control participant will give 80% power to detect a 0.7 log copies/ml difference between treatment groups (0.8 log copies/ml with 20% dropout).

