### 3. Analysis of data

The final analysis will be conducted once all randomized patients have completed completed the study as described OR one year following initiation of the study. There will be no interim analyses of efficacy data for the purposes of early study termination.

a) Patient characteristics

Patient characteristics at baseline will be summarized by randomized treatment using appropriate summary measures. Patient characteristics to be summarized will include age, sex, baseline CD4+ cell count and virus load. There will be no formal comparisons of baseline characteristics performed.

b) Efficacy parameters

All efficacy data will be analyzed by the intent-to-treat principle. In particular, all doses of SC IL-2 used in the escalation phase will be included in the data from treated patients.

The change from baseline in CD4+ cell count and virus load will be summarized at each sampling time point. Formal analysis will compare the randomized treatments in terms of time-weighted changes from baseline using ANOVA methods, or equivalent non-parametric methods as appropriate.

c) Safety

Safety data will be summarized by treatment received for each time point.

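### The overview promises virological neutrality, but HIV-RNA is sized and tested only for a difference, with no margin or interval rule, and that analysis cannot establish neutrality

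*Protocol*

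**What the plan says.** Protocol V.A (Overview) states the purpose in one sentence: "This protocol is intended to define the safety and tolerability, immunological superiority and virological neutrality of IL-2 immunotherapy over no therapy". The précis, the synopsis (I) and the objectives (IV) word the virological aim differently: to examine or assess effects on plasma HIV-RNA, without saying which result is expected.

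VIII.E.1 (Endpoints) makes "time-weighted mean change in plasma HIV-RNA from baseline" part of the primary endpoint, beside CD4+ count. VIII.E.2 (Sample size) assumes "within patient variability corresponding to a standard deviation of 0.7 log copies/ml". For 36 patients at 2:1 (IL-2 to control) it claims that the trial "will give 80% power to detect a 0.7 log copies/ml difference between treatment groups (0.8 log copies/ml with 20% dropout". VIII.E.3 (Analysis of data) gives one formal method for both endpoints: "Formal analysis will compare the randomized treatments in terms of time-weighted changes from baseline using ANOVA methods". Non-parametric equivalents are allowed, and changes from baseline are also summarised at each time point. Nowhere does the protocol give a margin for HIV-RNA or say how a confidence interval is to be read.

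**The concern.** Superiority and neutrality are different kinds of claim. Superiority is shown by finding a difference; neutrality is shown by excluding a rise large enough to matter. The protocol names both in one sentence and then gives CD4+ and HIV-RNA the same design, a two-sided test for a difference. That suits CD4+ and the softly worded HIV-RNA objective, but it does not suit neutrality.

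The protocol says that no clinical data exist on IL-2 without antiretrovirals (II.C) and that its effects in that setting are undefined (III), and it expects a phase III trial of 3700 patients to follow. If a null test were read as neutrality, a smaller or noisier trial would reach that reading more easily. Such a reading is foreseeable. In II.B the protocol describes an earlier subcutaneous trial as ending with HIV-RNA not significantly above baseline, and II.C then summarises three infusion trials as showing no sustained increase in virus load.

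**Working it through.** **Inputs.** From VIII.E.2: SD 0.7 log copies/ml, two-sided 5%, 36 patients at 2:1, 80% power for 0.7 log, and 0.8 log with 20% dropout. From V.A: 24 IL-2 (both doses pooled) and 12 control. With 20% dropout, 19.2 and 9.6 are evaluable.

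**1. Reproduce the plan's figure.**
- SE = SD × √(1/n₁ + 1/n₂) = 0.7 × √(1/24 + 1/12) = 0.7 × 0.3536 = 0.2475 log.
- Normal approximation: power at 0.7 log = Φ(0.7/0.2475 − 1.960) = Φ(0.868) = 80.7%. Noncentral t, 34 df: 78.5%.
- With dropout, SE = 0.7 × √(1/19.2 + 1/9.6) = 0.2767. Power at 0.8 log is 82.4% (normal) or 79.6% (t).

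The stated 80% is reproduced, so what follows rests on the protocol's own inputs.

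**2. Expected precision.** Half-width of the 95% interval = t(0.975) × SE.
- All 36 patients: 2.032 × 0.2475 = 0.503 log, a factor of 10^0.503 = 3.2.
- 20% dropout: 0.568 log, a factor of 3.7.

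If the observed difference were exactly zero, the upper limit would be about 0.50 log.

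**3. Chance of a non-significant result when HIV-RNA truly rises** (two-sided 5%, noncentral t).

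| True rise | 36 patients | 20% dropout |
|---|---|---|
| 0.3 log | 78% | 82% |
| 0.5 log | 50% | 59% |

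Under the normal approximation the 0.5 log entries are 48% and 56%. The 0.5 log rise is an illustration, because the protocol names no threshold. For scale, II.B reports transient two- to three-fold rises on day 5 of treatment, which is log₁₀2 = 0.30 to log₁₀3 = 0.48 log. Those are short-lived peaks and not time-weighted means.

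**4. Sensitivity to the SD** (true rise 0.5 log, 36 patients, t).

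| SD | Non-significant |
|---|---|
| 0.5 | 22% |
| 0.6 | 37% |
| 0.7 | 50% |
| 0.8 | 60% |

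**5. What a margin rule would deliver.** Suppose neutrality is concluded only if the upper 95% limit is below a margin M. For true difference D, the probability of that conclusion is the noncentral-t probability of exceeding t(0.975), with noncentrality (M − D)/SE.

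| Margin | D = 0, 36 patients | D = 0, 20% dropout |
|---|---|---|
| 0.7 log | 78% | 68% |
| 0.5 log | 50% | 41% |

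With M = 0.7, noncentrality is (0.7 − 0.5)/0.2475 = 0.81 at a true rise of 0.5 log, and neutrality would still be concluded in 12% of trials. At a true rise of 0.3 log it is 0.4/0.2475 = 1.62, and the figure is 35%. For 80% power at M = 0.5 and D = 0, the normal approximation gives 72 patients (48 + 24).

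**The case against.** The strongest reply is that neutrality is not the formal objective. The word occurs once, in an overview sentence, while the précis, synopsis and objectives speak of effects, and a two-sided difference test fits those. This stands. It means that rewording V.A is a full remedy for the mismatch. It does not make V.A consistent with the objectives as it is now written.

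A reader might infer that a real 0.5 log rise would be declared neutral half the time. The documents do not support that. No section says that a non-significant result will be called neutral. The 50% is the chance that the planned test is non-significant; a declaration of neutrality would need a decision rule that the protocol does not contain.

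A reader might also take 0.7 log as a ready-made neutrality margin. That is not supported either. In VIII.E.2 it is the difference that 36 patients can detect, and nobody has called it a tolerable rise. It is a five-fold increase (10^0.7), wider than the illustrative 0.5 log, and as step 5 shows it would not reliably exclude a rise of that size.

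Two further objections carry weight. This is a 36-patient open-label phase II study, the protocol attaches no go/no-go decision to a neutrality verdict, and a reporting rule could sit in an analysis plan that was not seen. That lowers the severity, but the aim, the sizing basis and the formal test are set in the protocol itself. Second, antiretrovirals may be started without restriction (VII.C.2) and analysis is by intent to treat. If they were started more often in the IL-2 arm because HIV-RNA rose, the difference would shrink. An interval or margin rule does not remove that.

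**Conclusion.** The point holds as a mismatch between one stated aim and the analysis provided for it. V.A claims neutrality; the objectives claim only to look at effects; VIII.E.2 and VIII.E.3 supply a difference test with no margin or interval rule. That analysis cannot establish neutrality. With the planned numbers the 95% interval reaches 0.50 log either side of the estimate (0.57 log with 20% dropout), and an illustrative true 0.5 log rise is non-significant 50% of the time (59% with dropout).

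These figures assume the protocol's SD of 0.7, the two IL-2 doses pooled as in VIII.E.2, and dropout unrelated to outcome. Over SD 0.5 to 0.8 the 50% becomes 22% to 60%. The conclusion that a non-significant test does not show neutrality depends on none of these values. Severity: should-fix.

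**What to change.** 1. In VIII.E.3, state that the HIV-RNA comparison is reported as the IL-2 minus control difference in time-weighted change with its two-sided 95% confidence interval, and that a non-significant p-value is not evidence of neutrality.
2. In VIII.E.2, add the expected half-width: 0.50 log with 36 patients, 0.57 log with 20% dropout.
3. Then do one of the following:
   - reword V.A to match the objectives and drop the claim of neutrality; or
   - keep the claim, and conclude neutrality only if the upper 95% limit is below a margin that the sponsor prespecifies and justifies, with its power stated. At zero true difference and 36 patients, power is 78% for 0.7 log and 50% for 0.5 log; with 20% dropout it is 68% and 41%.

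The cost is wording and a possibly less favourable claim. No more patients are needed for steps 1 and 2 or for either form of step 3. More would be needed only if the sponsor wanted 80% power at a margin tighter than 0.7 log.
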